**Walking planner**				
	Adding planner to people’s environment			007164
	Promotes habit formation			007094, 007096
	Promotes adapting plans as needed			007299
	If your days are different, try to develop a few different habits...			007010
	How many Active 10s are you aiming for			007003
	Plan: when and how much			007010
	Did you complete your plans?			007024
	How did you feel after you walked briskly?			007066, 007025
	Reminder not to worry if you miss a day and to adjust plans as required (reduce if finding it hard and increase if meeting goals and feel able).			007299
**Website**				
	Website and video branded from Yorkshire Cancer Research			007075
	Links to resources about the health benefits of physical activity			007183, 007181
	Links to resources to support walking (general walking websites and local information for areas recruiting from)			007042
	Promote physical and mental health benefits of brisk walking			007183, 007181
	Video: (1) promotes the physical and mental health benefits of brisk walking; (2) states that participants report enjoying using the app, liking having control and doing something for their health, and liking monitoring progress; and (3) shows a participant describing how they built up walking over time, made it part of their routine, and reported less physical pain and feeling emotionally better			007175, 007068, 007120, 007072, 007076
**Intervention: phone call or video call (1)**				
	Introduce self as working with clinical team at the hospital			007075
	Ask participants how their cancer and treatment have impacted their lifestyle and activity levels			
	Discuss physical and mental health benefits of physical activity			007183, 007181
	Discuss motivations to increase activity			007069
	Discuss concerns about increasing activity			007069, 007008
	Help participant to work out ways to overcome concerns about brisk walking, provide information as appropriate			007008
	Discuss why recommending brisk walking, including cancer patients have recommended this			007074
	Describe brisk walking			007058, 007051
	Provide information on government guidelines (150 minutes of MVPA^e^) as well as WHO^f^ Every Move Counts.			007075
	Highlight building up over time			007100
	Discuss how confident they are and how they can increase their confidence			007008
	Suggest trying it to see if that increases their confidence			007054, 007137
	If needed tell them that it is possible for them to do this and others have been able to			007137, 007076
	Promote habit formation for initiating a walk			007094, 007096
	Promote habit formation for planning walks, looking at app or planner			007094, 007096
	Make an action plan (when, what, how long)			007010
	Promote self-reward during or after walking			007257, 007252
	Promote nonspecific self-reward during or after walking			007257, 007252
	Promote using the app to track activity			007026
	Promote specific cues			007080, 007081
	Promote reminders			007080, 007081
	Promote adjustment of goals if needed			007011
	Promote adjustment of plans if needed			007299
	Set a target number of Active 10s			007300, 007010
	Promote asking friends to support, by encouraging and helping to remember to walk			007030, 007031, 007032, 007033
	Promote using the walking planner to track behavior			007024, 007025
	Encourage participants to use information provided to overcome their concerns about exercising			007008
**Intervention: phone call or video call (2)**				
	Remind them of their target, and discuss if needs adapting			007011
	Ask how they are getting on with their target			007012
	Ask participants what is preventing them from walking and what would help them to start (if relevant)			007008
	Repeat any of the points from call 1 as appropriate			As relevant

^a^BCTO item key: 007003 set behavior goal behavior change technique (BCT); 007005 set outcome goal; 007008 goal strategizing BCT; 007010 action planning; 007011 review behavior goal BCT; 007012 attend to discrepancy between current behavior and goal BCT; 007017 monitoring BCT; 007023 provide feedback on behavior; 007024 self-monitor behavior BCT; 007025 self-monitor outcome of behavior BCT; 007026 provide biofeedback BCT; 007029 advise to seek support; 007030 advise to seek instrumental support BCT; 007031 advise to seek emotional support BCT; 007032 advise to seek informational support BCT; 007033 advise to seek appraisal support BCT; 007042 deliver informational support; 007051 agree on how to perform behavior BCT; 007054 conduct a behavioral experiment BCT; 007058 instruct how to perform behavior; 007061 plan inclusion of enjoyment; 007063 inform about health consequences; 007065 inform about emotional consequences; 007066 monitor emotional consequences BCT; 007068 increase salience of consequences BCT; 007069 consider pros and cons BCT; 007072 awareness of other people’s thoughts, feelings, and actions BCT; 007074 increase awareness of others approval BCT; 007075 present information from credible influence BCT; 007076 suggest to change behavior BCT; 007077 tell to change behavior BCT; 007080 prompt intended action BCT; 007081 cue BCT; 007094 practice behavior BCT; 007096 context-specific repetition of behavior BCT; 007100 set graded tasks BCT; 007120 vicarious reward BCT; 007137 persuade about personal capability BCT; 007156 add objects to the environment BCT; 007164 add objects to the indirectly experienced environment BCT; 007168 advise specific behavior BCT; 007175 increase salience of behavior BCT; 007181 inform about positive emotional consequences BCT; 007183 inform about positive health consequences BCT; 007187 promise consequence for behavior BCT; 007209 promise positive material consequence for behavior BCT; 007211 promise positive material consequence for approximating behavior BCT; 007252 provide positive consequence for behavior BCT; 007253 provide positive consequence for approximating behavior BCT; 007254 provide positive consequence for completion of behavioral sequence BCT; 007257 provide positive material consequence for behavior BCT; 007299 review behavior goal plan BCT; and 007300 set measurable behavior goal BCT.

^b^NHS: National Health Service.

^c^N/A: not applicable.

^d^UCL: University College London.

^e^MVPA: moderate-to-vigorous physical activity.

^f^WHO: World Health Organization.

Several BCTs have shown promise in systematic reviews and meta-analyses focused on increasing PA in inactive adults [49] and specifically after cancer, including adding an object to the environment, self-monitoring, goal setting [64], action planning, social support [65], and rewards [66]. This study focused on BCTs that were considered to have efficacy in this population and those practical to use in the context of an app-based intervention with brief behavioral support.

Intervention participants are mailed a pack containing a clinician endorsed letter, alongside printed materials (leaflet and walking planner cards) and an appointment time for a behavioral support video or telephone call. Since the trial is ongoing at the time of writing this protocol, intervention materials are not included, but the mapping exercise is provided (Table 3) and further detail is available upon request from the corresponding author.

#### Leaflet and Website

The leaflet covers topics including the benefits of PA during or after cancer treatment (eg, reduces side effects), introduces how walking and particularly brisk walking counts as moderate PA (encouraging individuals to gradually build up), and walking habits (eg, importance of repetition, planning walking into daily routines). The leaflet also introduces the NHS Active 10 app (including how to download it), and has a link to the study website (not used in the pilot as all information was included in the leaflet because the pilot was conducted in one location), which contains copies of all the study resources and also local area-specific resources relating to walking groups or places to walk, which were accumulated by doing internet searches of walking resources in these areas (eg, Get Doncaster Moving council initiative, 5k Your Way). The website used in the randomized controlled trial also includes a brief film of participants from the pilot [53] who used the app and increased their walking.

#### Walking Planner Cards

The walking planner cards are underpinned by BCT principles and habit theory that have been shown to increase PA, including a focus on helping participants set goals (eg, “How many daily Active 10s are you aiming for?”), plan their walks (action planning, eg, “On Monday I will walk:…”), and self-monitor (eg, “Tick when you complete each plan”). These cards were amended based on feedback from pilot participants [53], many of whom felt they were too restrictive. The core content remained (eg, prompting the time of day or situation), but the redesign enabled more flexibility for different plans on different days of the week.

#### App

The NHS Active 10 app is publicly available, developed by Public Health England [48], and currently maintained by the Department of Health and Social Care. This app was selected based on extensive development work [46,52,67], plus patient and public involvement (PPI) and pilot study results [53]. The app incorporates BCTs such as goal setting, self-monitoring behavior, and prompting practice of behaviors [68,69].

The app tracks all walking activity and provides a total for time spent walking and time spent brisk walking. Ten minutes of brisk walking is known as one “Active 10.” The app encourages users to initially build up to completing one Active 10. Users can set a goal to complete 1-3 Active 10s per day, with the aim of reaching 30 minutes, and if successful they can set up to 5 Active 10s. Each individual minute of brisk walking is recorded and contributes to the Active 10s (to fit with current UK Chief Medical Officers’ PA guidance that updated the previous recommendation that a minimum 10-minute bout of activity was required [70]). Moderate activity has been shown to provide greater health benefits than slower-paced walking [71]. The app uses the mobile phone’s inbuilt sensors to measure activity and record the total minutes of walking and, where relevant, brisk walking (100+ spm).

Since the pilot study was completed, a “pace checker” function has been added, enabling users to see timed pulses on the app (in line with 100 spm) while walking for a 1-minute period and, at the end of the 1 minute, shows the number of steps achieved and whether it was classed as brisk. Figure 2 illustrates some screenshots from the app, including the new feature.

**Figure 2 figure2:**
[figure not shown]
Screenshots of Active 10 app.

#### Behavioral Support Calls

Two semiscripted behavioral support video or telephone calls are undertaken by a trained researcher around one month apart. The first call takes place as soon after randomization as possible and introduces the recommendations around PA for people diagnosed with cancer (eg, 150 minutes of MVPA), how brisk walking is a form of moderate PA, the evidence for benefits of meeting these guidelines, and the importance of increasing PA by any amount (eg, highlighting the Every Movement Counts World Health Organization campaign) [72]. The researcher also explains how to form walking habits, how the app works, and encourages use of the app to help set and monitor goals (eg, “What do you want to aim for? One, two or three active tens [so 10, 20 or 30 minutes of brisk walking a day]”). Participants are encouraged to make plans and establish habits for using the app, plan to increase their brisk walking if appropriate, and use the app to track their progress. The call also aims to explore barriers to PA and explore ways of addressing them drawn from evidence (eg, treatment-related fatigue). This call is intended to replicate the type of conversation that a health care professional (eg, clinical nurse specialist) could have with patients as part of routine care. A second call is arranged for around 4 weeks later to see how participants are progressing, troubleshoot (eg, their plans or the app), and remind and recap on any information as required. With the participant’s agreement, calls are recorded to allow fidelity checks.

### Control Group

Control group participants are notified of their group allocation by telephone or email, then receive “usual care” (no additional support beyond being informed in the information sheet that PA is beneficial for people after a diagnosis of cancer).

### Measures

#### Overview

For all assessments, participants are emailed a link to a questionnaire on REDCap [57,58] and mailed an activPAL. If participants consented to provide body measurements, they are also mailed a set of weighing scales (Seca 803 if they weigh less than 150 kg; Seca 813 if they weigh over 150 kg) and a tape measure (Seca 201) at baseline. Reminder calls are made if any questionnaires are not completed, and telephone support on completing the questionnaires is provided where necessary. To be included in analysis, 3-month data must be completed between 12-18 weeks postrandomization and 6-month data between 24-30 weeks postrandomization. Researchers involved in collecting follow-up assessment data are blinded to group allocation.

#### Sociodemographic Characteristics and Disease Characteristics

At baseline, age, sex, employment and education status, marital status, living arrangements, postcode, and ethnicity are self-reported. Participant’s postcodes will be used to determine socioeconomic position using the Index of Multiple Deprivation [73]. Participants are asked to self-report their cancer diagnosis and comorbid health conditions [74] at baseline, and clinical details will be verified from medical records (including diagnosis date and stage and treatment received).

#### Physical Activity

PA is measured objectively [75] using thigh-worn activPAL accelerometer (sent with detailed instructions and materials to apply the device to their thigh, plus a link to a video of a researcher demonstrating how to attach the device). Participants are asked to wear the activPAL for 7 days continuously at each timepoint (ie, baseline, 3 months, and 6 months). ActivPAL data will be used to calculate the primary endpoint. Participants will also complete a log sheet recording when the device was worn and their bedtimes and waketimes. ActivPAL devices have been used successfully in other studies, including those diagnosed with cancer [76], and were used in the pilot [44,53]. The primary endpoint is activPAL-assessed average minutes of brisk walking (≥100 spm) 3 months after randomization (controlling for baseline rates). ActivPAL data will also be used to assess brisk walking at 6 months, average total steps, minutes of light PA, standing time, sitting time, and weekly MET. Participants will also complete the Godin Leisure Time Exercise Questionnaire (GLTEQ) [77], which has demonstrated favorable validity and reliability against objective measures of PA and is widely used in oncology research [78]. This questionnaire was adapted in the pilot [44,53] to include a question about duration of activities to allow the calculation of minutes of MVPA [78].

#### Anthropometric Outcomes (Optional)

Height, weight (without outer clothing or shoes on), and waist circumference (at the umbilicus) are self-reported by participants into an online questionnaire. Previous studies have illustrated that self-reported weight and waist circumference are adequately reliable and accurate where objective measurement is not possible [79-81]. BMI will be calculated using the standard formula of weight (kg) ÷ height (m)^2^. Participants who provide these measures at baseline will keep the weighing scales and tape measure for the later follow-ups.

#### Psychosocial Variables

To assess the broader impact of the intervention, the psychosocial variables outlined in Table 4 are self-reported at each timepoint.

**Table 4 table4:** Details of the psychosocial variables and measures included in the questionnaires.

Construct	Measure	Reliability and validity references
Health related quality of life (HRQoL)	EQ-5D-5L and visual analogue scale [82]	Reliable and valid among patients with cancer [83]
Cancer-specific quality of life	27-item Functional Assessment of Cancer Therapy-General (FACT-G) scale [84]	Good validity and reliability [84]
Fatigue	13-item fatigue subscale of the Functional Assessment of Chronic Illness Therapy-Fatigue (FACIT-F) [85]	A brief reliable and valid measure [85]
Sleep quality	18-item Pittsburgh Sleep Quality Index (PSQI), which assesses sleep quality and disturbances over a 1-month time interval [86]	Used extensively in clinical (including cancer) and nonclinical samples, with good reliability and validity [87]
Anxiety	7-item Generalized Anxiety Disorder-7 (GAD-7) Assessment [88]	Adequate diagnostic accuracy in patients with cancer [89]
Depression	9-item Patient Health Questionnaire (PHQ-9) [90]	Adequate diagnostic accuracy in patients with cancer [91]
Physical activity self-efficacy	13-item Physical Activity Appraisal Inventory (PAAI)	Reliability and validity in women with breast cancer [92]
Self-efficacy to self-manage cancer	11-item Cancer Survivorship Self-Efficacy Scale (CS-SES) [93]	Excellent reliability across mixed patients with cancer [93]
Habit strength for walking	4-item Self-Report Behavioral Automaticity Index (SRBAI) [94], which will be measured focusing on “going for a walk” and “walking briskly”	Good reliability and sensitivity to changes in habit [94]
Social support	6-item brief form of the Perceived Social Support Questionnaire (F-Soz-U K-6) [95]	Good reliability and validity across the lifespan [95]

To conduct exploratory analysis between the activPAL data and habit strength, investigating whether those who walk in the morning have higher habit strength than those who walk in the evening, participants will be asked 4 questions related to their chronotype (individual differences in sleep timing and in preferences for sleeping at given times of day). This will be measured using a subscale of the Morningness-Eveningness Questionnaire [96] used by Randler et al [97], with the English wording taken from Terman et al [98]. Additionally, 2 items (scored on a 5-point Likert scale) from the Creature of Habit scale [99] will be used to assess preference for routine (“I tend to like routine” and “I find comfort in regularity”).

#### Health and Social Care Service Use

Participants are asked to self-report their use of health and social care using items from the Client Service Receipt Inventory (CSRI), which has been validated against objective primary care records [100] and is recommended for usage of hospital and other community health services [101]. As part of the medical records data collection (undertaken by research staff at 6 months postrandomization), details about participant’s hospital-based treatment and care received (including the number of hospital contacts) during the 30-week trial period will be recorded.

#### App Use and Physical Activity Changes

No data collected by the app itself will be obtained by the research team [53] owing to the app data not being stored in a way that would allow linkage with our trial participants. Therefore, participants in both groups are asked to report their use of any PA apps during the study period, whether they have done anything to change their PA since starting the trial, and what prompted them. Additionally, intervention group participants complete brief feedback questions on the intervention content in the follow-up questionnaires, self-report their usage of the app, and complete the Digital Behavior Change Interventions Engagement Scale [102], which was used in the pilot study to capture app engagement [53]. A single item (“How accurately do you think the app recorded the amount of time you spent walking [the total minutes and brisk minutes]?”) about perceived accuracy of the app is included at 6 months (5-point scale, 1=not accurate and 5=very accurate).

#### Qualitative End of Study Interviews

A subsample of intervention participants (approximately n=20-30) will be interviewed after they have completed the 6-month data collection. These telephone or video call interviews will be semistructured (Multimedia Appendix 4 provides the interview guide), audio recorded, and will explore experiences of using the intervention materials, their walking experiences, and their use of the app.

### Data Analysis

The primary endpoint, the difference between trial arms in change from baseline in activPAL-assessed average minutes of brisk walking (≥100 spm) 3 months after randomization, will be analyzed by a statistician blind to intervention allocation on an intention-to-treat basis. Estimates of effect sizes will be presented with 95% CIs and 2-sided 5% *P* values. The statistical analysis plan will be finalized prior to completion of data collection. Cross-sectional analysis will be performed at 3 months (primary endpoint) and 6 months (secondary endpoint) using linear regression to compare the two trial arms, with baseline time spent walking at ≥100 spm included as a covariate. Generalized linear mixed models will also be used to model repeated measurements over time, with individual patient random effects, and intervention, time, and intervention-by-time interaction fixed effects. Other continuous secondary outcomes (ie, average daily total steps, minutes of light PA, standing time and sitting time, GLTEQ, EQ-5D-5L, Functional Assessment of Cancer Therapy-General [FACT-G], Functional Assessment of Chronic Illness Therapy-Fatigue [FACIT-F], Pittsburgh Sleep Quality Index [PSQI], Generalized Anxiety Disorder-7 [GAD-7], Patient Health Questionnaire-9 [PHQ-9], Physical Activity Appraisal Inventory [PAAI], Self-Report Behavioral Automaticity Index [SRBAI], BMI, and waist circumference) will be analyzed using a similar approach. Relationships with baseline participant and disease characteristics will be investigated through covariates for main effects as well as interactions with the trial intervention. Subgroup analyses will be performed by stratification factors used in the randomization procedure and presented using forest plots and *P* values from interaction tests. Exploratory analyses to understand the role of habit strength as a mechanism in the relationship between the trial intervention and PA will be carried out through further regression modeling.

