### Sample Size

The APPROACH pilot study data [53] were used to inform this power calculation. The target sample size is 472 participants randomized 1:1 to detect a difference between trial arms in the change from baseline in the daily average of 6 minutes per day (ie, 42 minutes per week) of activity at 100 spm or higher. This assumes 90% power, a 2-sided 5% significance level, an SD of 12 minutes per day in the control arm, and a variance ratio of 1:4 (control:intervention). Low attrition (3%) was observed in the pilot, but with multiple recruiting sites and longer follow-up, a 10% attrition rate has been allowed to ensure the required 212 participants per arm is achieved.

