### Randomization

Post baseline data collection, participants are individually randomized using minimization with a 1:1 allocation ratio by the central trial team at UCL (a researcher not involved with recruitment or data collection) using code developed by a UCL senior research data scientist, based on the paper by O’Callaghan [59], which is available on GitHub [60]. Stratification factors are cancer type (breast, prostate, colorectal) and hospital site. The first participant is randomly allocated; thereafter, subsequent participants are assigned based on the arm with the lowest imbalance score while factoring in a 20% random element. Randomization constitutes full enrollment in the trial.

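### The stated primary regression does not include the minimisation factors (cancer type, hospital site); if they predict outcome beyond baseline, its reported SE and CI are conservative

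*Protocol article*

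**What the plan says.** **Allocation (Randomization).** The article says that "participants are individually randomized using minimization with a 1:1 allocation ratio", and that "Stratification factors are cancer type (breast, prostate, colorectal) and hospital site". After the first participant, each person is "assigned based on the arm with the lowest imbalance score while factoring in a 20% random element".

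**Primary model (Data Analysis).** The 3-month and 6-month comparisons are made "using linear regression to compare the two trial arms, with baseline time spent walking at ≥100 spm included as a covariate". No other covariate is named. The repeated-measures model is listed term by term: patient random effects, intervention, time and their interaction. The minimisation factors are not among the terms. The other continuous secondary outcomes are to be analysed along similar lines.

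**Where the factors do appear (Data Analysis).** "Subgroup analyses will be performed by stratification factors used in the randomization procedure", with forest plots and interaction tests. Separately, "Relationships with baseline participant and disease characteristics will be investigated through covariates for main effects as well as interactions with the trial intervention". Cancer type would naturally fall under that second statement, but it describes further modelling and not the primary comparison.

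**Status of the analysis plan.** "The statistical analysis plan will be finalized prior to completion of data collection". It is not among the documents at hand.

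**The concern.** Minimisation makes the arms more alike on cancer type and site than simple randomisation would. Whatever those factors contribute to 3-month brisk walking then largely cancels out of the arm difference, and the estimate varies less from trial to trial. A regression without the factors cannot see this. It leaves their contribution in the residual and reports the SE that simple randomisation would have produced.

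At stake is the accuracy of the reported SE, CI and P value for the primary endpoint and, if the same terms are carried over, for the 6-month, repeated-measures and continuous secondary analyses. The direction is known: intervals too wide and a test that rejects less often than its nominal 5%. The size depends on how much the factors predict beyond baseline brisk walking, which the article does not say.

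**Working it through.** **Inputs from Sample Size.** Difference of 6 minutes per day in change from baseline; two-sided 5%; 90% power; control SD 12; variance ratio 1:4, so intervention SD = 12 × √4 = 24; 10% attrition; 212 per arm; 472 in total.

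**Reproducing the plan's figure.** n per arm = (12² + 24²)(1.960 + 1.2816)² / 6² = 720 × 10.507 / 36 = 210.15, so 211. With unequal-variance t-test power, 211 gives 89.94% and 212 gives 90.07%, so 212 is the first size to reach 90%. Then 212 / 0.9 = 235.6, so 236 per arm and 472 in total. The stated figures reproduce.

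**Assumptions.** R2 is the share of outcome variance, after baseline adjustment, that cancer type and site explain. It is not in the document, so a range from 0 to 20% is shown. The stated SDs are taken as residual SDs after baseline adjustment. The factors are taken as essentially balanced.

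**Formulas (normal approximation, 212 per arm).**
- Reported SE without the factors: √(720 / 212) = 1.843, whatever R2 is.
- True sampling SD: s = 1.843 × √(1 − R2). A model with the factors reports this as its SE.
- CI width relative to the correct width: 1 / √(1 − R2).
- Type I error without the factors: 2[1 − Φ(1.960 / √(1 − R2))].
- Power without: Φ((6 − 1.960 × 1.843) / s). Power with: Φ(6 / s − 1.960).

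Worked at R2 = 10%: s = 1.843 × 0.9487 = 1.748. Type I error = 2[1 − Φ(2.066)] = 3.9%. Power without = Φ(2.388 / 1.748) = Φ(1.366) = 91.4%. Power with = Φ(3.432 − 1.960) = Φ(1.472) = 93.0%.

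| R2 | SE without | SE with | CI too wide by | Type I error without | Power without | Power with |
|---|---|---|---|---|---|---|
| 0 | 1.843 | 1.843 | 0% | 5.0% | 90.2% | 90.2% |
| 2% | 1.843 | 1.824 | 1.0% | 4.8% | 90.5% | 90.8% |
| 5% | 1.843 | 1.796 | 2.6% | 4.4% | 90.8% | 91.6% |
| 10% | 1.843 | 1.748 | 5.4% | 3.9% | 91.4% | 93.0% |
| 20% | 1.843 | 1.648 | 11.8% | 2.8% | 92.6% | 95.4% |

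Anchoring at exactly 90% power instead of the 90.2% that 212 per arm gives on this approximation shifts the power figures slightly: 90.6% and 91.4% at R2 = 5%, 91.2% and 92.7% at 10%.

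**Simulation check.** Minimisation on both factors, with 20% of allocations made at random, was simulated with 424 participants, an assumed 10 equal sites and an assumed 45/30/25% cancer mix (3,000 runs per setting).

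| R2 | Empirical SD, without / with | Mean model SE, without / with | Type I error, without / with | Power, without / with |
|---|---|---|---|---|
| 0 | 1.845 / 1.845 | 1.843 / 1.844 | 4.9% / 5.0% | 89.9% / 90.0% |
| 10% | 1.743 / 1.741 | 1.842 / 1.747 | 3.6% / 4.8% | 91.0% / 92.9% |
| 20% | 1.647 / 1.641 | 1.843 / 1.649 | 3.1% / 4.8% | 92.5% / 95.5% |

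At R2 = 5% these runs gave power of 89.0% without and 90.0% with the factors, below the formula. Monte Carlo error is about √(0.9 × 0.1 / 3000) = 0.5 points. A repeat of this setting with 12,000 runs gave 90.6% and 91.5%, in line with the table, so the low values were chance.

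The empirical SDs are nearly equal with and without the factors. The estimate therefore already has the precision; only the SE reported by the model without them is too large.

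**The case against.** The strongest reply is that the article condenses a fuller protocol and points to a statistical analysis plan that is not shown. Naming one covariate does not exclude others, and the handling of randomisation factors and small sites is often settled in that plan. This stands in part. A reader might infer that baseline brisk walking is the sole covariate, or that the factors are ignored in all modelling. The documents support neither reading: the text does not say sole, the factors are used in subgroup and interaction analyses, and cancer type fits the planned work on disease characteristics. What remains is that the article does more than stay silent. It states a model, names a covariate for it, and mentions the minimisation factors in another role. Someone working from it would fit baseline-only regression.

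The second reply is that the consequence is conditional. This stands fully. Baseline brisk walking in the same person may already carry most of what cancer type and site would predict, and R2 may be close to 0, in which case model and design agree.

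The third is that the effect is small and in the safe direction. This also stands. It limits the weight of the point but does not remove the mismatch.

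**Conclusion.** The point holds in a limited form: the primary model as published does not match the allocation scheme as published. If cancer type or site predicts 3-month brisk walking beyond baseline, the reported SE and CI are too wide and type I error is below 5%. Over R2 from 0 to 20%, type I error runs from 5.0% to 2.8%, and the power forgone from 0 to about 3 points (95.4 − 92.6 = 2.8).

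A reader might go further and conclude that the primary P value is miscalibrated as a matter of fact, that the trial is underpowered, or that false positives are inflated. None of these follows. The documents give no R2; power by formula stays at or above the planned 90% throughout; the error is conservative and the effect estimate is not biased. The target of 472 does not change.

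The figures rest on the plan's SDs standing for residual SDs after baseline adjustment, on near balance of the factors, and, for the simulation, on an assumed number of sites and cancer mix. The change is worth making because it costs almost nothing, not because the trial is at risk without it.

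**What to change.** State the primary 3-month model as brisk walking on arm, baseline brisk walking, cancer type and hospital site. Site can be a random intercept, or a fixed effect with very small sites pooled by a rule set in advance. Carry the same factors into the 6-month comparison, the repeated-measures model and the continuous secondary outcomes. Settle this before unblinding. The baseline-only regression can be kept as a sensitivity analysis. If the statistical analysis plan already includes the factors, the only step is to align the published description with it.

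The cost is about one sentence. No new data are needed, since both factors were used to allocate every participant. The loss is 2 degrees of freedom for cancer type and, with fixed effects, one fewer than the number of sites: 2 + 9 = 11 of 424 with an assumed 10 sites.
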